## Abstract

**Background:**

Alcohol misuse is a serious problem among university students in Colombia as well as in other Latin American countries. Studies show consistently that this population presents the highest rates of alcohol use. Despite such a situation, there is a lack of preventive programs for university students in this region of the world. The purpose of this paper is to present the protocol to evaluate a preventive strategy called IBEM-U, based on Motivational Interviewing and the I-Change Model.

**Method:**

This protocol shows how the evaluation of the effectiveness of the IBEM-U program will be carried out. A randomized control trial with a within-subjects design with one follow-up at six months after the post-test will be implemented. The comparison group will receive an alternative program similar in length but focusing on another issue. Around 1000 participants over 18 years of age, from at least six different universities around the country, will be recruited.

**Results:**

It is expected that the program will be effective in reducing past month alcohol consumption up to 15% in the experimental group as the main outcome. Secondary and tertiary outcomes include decreasing heavy episodic drinking and increasing knowledge, awareness, risk perception, attitude, self-efficacy, intention, and action planning, regarding heavy episodic drinking.

**Conclusion:**

IBEM-U can be considered a highly appropriate approach for reducing alcohol misuse among university students. The main reasons for these results are the self-imposed goals based on long-term purposes, that could be seriously affected by the ingestion of high amounts of alcohol.

## Introduction

1

### The problem of alcohol consumption

1.1

Alcohol misuse leads to several mental, physical, academic, and social problems in young adults. Among those problems, the most relevant are depression and suicidal ideation [1]; negative impacts on the immune and digestive systems, damage of the liver resulting in fibrosis or cirrhosis, as well as the link to 25 different types of cancer in the long term [[2], [3], [4]]; higher risk of unwanted pregnancies and sexual transmission infections [5,6]; a progressive decline in cognitive skills and processes of memory and planning, as well as a loss of capacity for decision-making [8,9]; National Institute on Alcohol Abuse and Alcoholism [ [10,11]. Regarding social problems, prior studies have found that high levels of drinking, especially among youth, can act as a risk factor for becoming a victim or perpetrator of violence (Pan American Health Organization [12].

Although Heavy Episodic Drinking^1^ (HED – defined as ten or more standard drinks per occasion at least once in the past month) has decreased worldwide (diminishing from 47.6% in 2000 to 43% in 2016 for current drinkers, and from 22.6% in 2000 to 18.2% in 2016 for heavy episodic drinkers), alcohol use among young adults remains a public health problem (World Health Organization [13]. The Americas region (North and Latin America) has the second highest rates of alcohol use among young adults aged between 20 and 24 years (38.2%), after the European region (43.8%) [14]. Data on excessive drinking are particularly high among university students in the Americas, pointing out that HED in the past month, corresponded to 18.6% among Latin American university students; Colombia, Uruguay, Ecuador, and Brazil have the highest levels of alcohol consumption (Organization of American States [15]. The same report states that between 60% and 87% of the Latin American university population perceived alcohol use as a severe risk to for intoxication; nevertheless, they continue excessive drinking. In Colombia, university students have the highest rates of alcohol use: 55.4% report using alcohol in the past month, compared with 38.4% of 18 to 24-year-olds and 39.7% of 25 to 34-year-olds in the general population (Comunidad Andina de Naciones [16].

HED is a common practice among university students in Colombia; the usual pattern according to Ref. [17] is biweekly or monthly (58.1% of those who show HED). Among students, 85% drink especially in discos and bars, mainly with friends, and about 30% drink at friends’ homes. There are no significant differences in drinking patterns between young men and women [17,18]. The involvement of the students in HED has several reasons, such as widespread availability of alcohol nearby the facilities, high social pressure to drink, leisure time between classes, and increased stress due to new academic demands [10,19]. In spite of the difficulty to find effective strategies to work with this population, prevention appears to be the most logic and potentially most productive way to tackle the situation.

### Preventive interventions

1.2

Alcohol use prevention, including HED, in universities has been addressed through multiple modalities. Online interventions are one such modality, although specific interventions have varied in length and delivery format [20]. Some online brief alcohol interventions have been created to deliver feedback once the person fills out a questionnaire [21]. Other interventions promote responsible decision-making regarding alcohol use: different scenarios are presented to the participant for them to choose the best option and they then receive feedback based on their choice [22]. There are also interventions which are carried out entirely by email [23]. Although those online programs reach more people compared to face-to-face interventions, they lack feedback sufficiently tailored to the participants’ realities, adjusted to what participants know and believe about alcohol and drug consumption [20]. They also have been criticized for lacking persuasive theoretical approaches, including awareness of risks about certain behaviors, especially culturally-normative behaviors such as alcohol consumption.

In this protocol we describe a new preventive intervention for university population which uses the I-Change Model [24] as theoretical framework, and Motivational Interviewing [25]; 2013 [26]; as the method. Both approaches have shown effectiveness in facilitating behavior change: In a meta-analytic review [27], found that face-to-face interventions based on Motivational Interviewing reported more extended periods of fewer problems related to alcohol abuse (up to six months); they also mention that this approach could be considered one of the most efficacious for university students who have had episodes of heavy drinking. Another meta-analysis (Kohler & Hofmann, 2014) observed that Motivational Interviewing was more effective than other approaches in reducing frequency and quantity of alcohol consumption among young people. Regarding the I-Change Model, a randomized control trial showed that those adults who received the intervention with this theoretical framework decreased 3.9 drinks weekly, compared to the control group, in a follow-up six months after the intervention (Shulz et al., 2013). Other studies have demonstrated the efficacy of this approach among other populations, such as adolescents [28], and pregnant women six months after baseline [29]. Both approaches also acknowledge the importance of raising awareness of the problems associated with alcohol misuse, increasing motivation to adopt a healthier behavior, setting goals for change, and developing action plans for enacting the desired healthy behavior. The I-Change model offers clear steps to increase awareness (e.g. to increase cognizance about the level of drinking and knowledge about the risks of drinking), to enhance motivation (e.g. by developing a positive attitude, positive norms and self-efficacy), and to develop clear action and coping plans [28,30]. Motivational interviewing will be used to provide the didactic framework for the intervention by focusing on providing empathy, developing discrepancy, rolling with resistance, and supporting self-efficacy. Both models will serve as the theoretical underpinning for this intervention IBEM-U (acronym in Spanish of *Intervención Breve basada en Entrevista Motivacional* - Brief Intervention based on Motivational Interviewing for University students).

In Colombia, the combination of these approaches with this population in an online intervention has not been used before. Moreover, there are only six evaluated programs, all of which are addressed to adolescents from secondary school; programs for university students do not exist in the country [31,32].

IBEM -U is an online prevention program for university students and is based on our previously created and evaluated face-to-face IBEM program for adolescents; IBEM showed significant effects on decreasing alcohol consumption [33,34]. A pilot was conducted in 2020 with 60 students, and adjustments were made mainly to the platform. This paper describes the study protocol of the IBEM-U program (main intervention) to assess its effects on decreasing alcohol consumption and heavy episodic drinking among university students.

## Methodology

2

### Study design

2.1

The effectiveness of IBEM-U to reduce problem alcohol use will be analyzed using a randomized control trial with a within-subjects design with one follow up at six months after the post-test. The intervention group will receive IBEM-U, the comparison group will receive an alternative program similar in length but focusing on learning strategies (EDA – acronym in Spanish of *Estrategias De Aprendizaje* –), aimed at promoting the use of strategies to facilitate the learning process in general. A baseline measurement (T0) will be obtained before randomization; a second measurement will occur at the end of the program (T1) – (three months after baseline); and a follow-up at six months after the second measurement (T2) (nine months after baseline).

### Goals and hypotheses

2.2

The main goal of the RCT is to evaluate the effects of an adaptive program aimed at reducing frequency and quantity of alcohol use, among young adults from different universities in Colombia, compared to a control group, immediately after its implementation and six months later. The primary outcome is the number of standard drinks consumed in the past month. We hypothesize that the IBEM-U program will be effective in reducing past month alcohol consumption in undergraduate and graduate adult students, up to 15% in the experimental group. Secondary outcomes are decreasing heavy episodic drinking up to 10%. Tertiary outcomes include changes related to knowledge, awareness, risk perception, attitude, self-efficacy, intention, and action planning, regarding heavy episodic drinking.

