#### Sample size

2.5.1

Sample size was determined using a simulation-based power analysis (1000 simulations), with Superpower package [37] for R, version 4.0.3 [38]. We hypothesized means for intervention and control groups for each measure with a SD of 5 and a r = 0.2 for repeated measure variables. This will mean an estimate of an effect size for group (*f* = 0.037), measurement (*f* = 0.048) and interaction between group and measurement 1-β = 0.90. The recommended *N* for each group is 191 (see). Considering the possible attrition rate of about 50%, it is planned to recruit 764 participants.

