This research has some possible limitations. First, since it is a modular intervention (using universal and/or selective prevention strategies) that is adapted to the risk level of the individual participant, many of whom will have low levels of alcohol use, it may not be possible to see significant reductions in Heavy Episodic Drinking. However, a decrease in overall alcohol consumption will still be able to be examined. Second, online interventions at universities are not common in Colombia, and it might result in high dropout rates. To counter this, there will be a raffle of several latest-technology tablets for those who complete all three measurements, and participants will receive reminders about the sessions. Third, the COVID 19 pandemic had many social impacts, not only in terms of alcohol use patterns and circumstances, but also affected recruitment for studies such as this one. The research team will try new strategies to recruit and retain participant across all three waves of data collection.

Conclusion: IBEM-U can be considered a highly appropriate approach for reducing alcohol misuse among university students. The main reason for this result is the self-imposed goals formulated based on long-term purposes that could be seriously affected by the intake of high amounts of alcohol.

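### The stated 90% power does not apply to the hypothesised 15% reduction in past-month drinks; at the cited drinking prevalence and the planned r = 0.2 it is at most about 25%

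*Protocol article*

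**What the plan says.** Section 2.2 (Goals and hypotheses) defines the outcome: "The primary outcome is the number of standard drinks consumed in the past month". The hypothesis is that the programme will be "effective in reducing past month alcohol consumption in undergraduate and graduate adult students, up to 15% in the experimental group". The same section sets the goal as a comparison with the control group, straight after the programme and six months later.

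Section 2.5.1 (Sample size) reads: "We hypothesized means for intervention and control groups for each measure with a SD of 5 and a r = 0.2 for repeated measure variables". It prints effect sizes of 0.037 for group and 0.048 for measurement, both labelled *f*, and then "interaction between group and measurement 1-β = 0.90". The result is 191 per group, or 764 recruited after 50% attrition. The text shown contains neither the hypothesised means nor a baseline mean, and it does not connect the calculation to 15%.

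Three other places bear on how much the participants drink:
- Section 1.1 says of Colombian university students that "55.4% report using alcohol in the past month".
- The inclusion criteria in section 2.3 contain no drinking requirement.
- The Discussion expects participants "many of whom will have low levels of alcohol use".

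**The concern.** A reader will take the 90% as the chance of detecting the hypothesised 15% reduction. A percentage becomes a number of drinks only through a mean, and the power of that difference depends on the ratio of mean to SD. When many participants score zero on a non-negative outcome, the SD cannot be small relative to the mean. The SD of 5, the 15% target and the cited prevalence may therefore be unable to yield 90% power together.

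If so, a true 15% effect could well give a non-significant result and be read as failure of a programme that section 3 says will be offered to the Colombian government.

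**Working it through.** **Inputs.** SD 5, r = 0.2, 191 per group and power 0.90 (section 2.5.1); three measurements (2.1); 15% (2.2); 55.4% past-month drinkers (1.1). Alpha is not stated, so 0.05 is assumed.

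**1. Reproducing the plan's figure.** For a 2 × 3 mixed ANOVA with compound symmetry, the interaction noncentrality is λ = (n/2) · Σ(d_t − d̄)² / [SD²(1 − r)], where d_t is the group difference at time t.
- With differences of (0, 2, 2) drinks, Σ(d_t − d̄)² = 8/3. Then λ = 95.5 × 2.667 / (25 × 0.8) = 12.73 on 2 and 760 df, and power is 0.9007. At n = 190 it is 0.8991, so 191 is the smallest n that reaches 0.90.
- Group effect: λ = 95.5 × (4/3)² / (25 × 1.4/3) = 14.55. Partial η² = 14.55/(14.55 + 380) = 0.037.
- Measurement effect, with overall means falling one drink per wave: λ = 382 × 2/20 = 38.2. Partial η² = 38.2/(38.2 + 760) = 0.048.
- 382/(1 − 0.5) = 764.

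A two-drink difference at both follow-ups thus recovers n, power and both printed effect sizes, if those are read as partial η². As Cohen's *f* the same effects would be 0.196 and 0.224.

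**2. What mean makes 2 drinks equal to 15%?** 2/0.15 = 13.3 drinks a month. With SD 5 the coefficient of variation (CV) is 5/13.3 = 0.375.

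**3. What the prevalence allows.** If a share p drink and the rest score zero, SD ≥ mean × √((1 − p)/p), with equality only if all drinkers drink the same amount. At p = 0.554 the factor is √(0.446/0.554) = 0.897.
- SD 5 caps the mean at 5/0.897 = 5.57, and 15% of that is 0.84 drinks.
- A mean of 13.3 needs an SD of at least 13.3 × 0.897 = 12.0.
- Whatever the SD, 15% is at most 0.15/0.897 = 0.167 SD.
- A CV of 0.375 needs p ≥ 1/(1 + 0.375²) = 87.7% drinkers, all drinking alike.

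**4. Power for 15% at that bound.** λ = 95.5 × 0.167² × (2/3)/0.8 = 2.22, giving power 0.246 (simulation 0.243). A 1-df pre-post contrast gives 0.252. Reaching 0.90 would take about 1,090 (2 df) to 1,200 (1 df) completers per group.

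**5. How far this moves.** Interaction test with 191 per group unless noted; no variation among drinkers except in the last two rows.

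| Setting | Maximum power for 15% |
|---|---|
| 55.4% drinkers, r = 0.2 | 0.25 |
| same, single-time-point ANCOVA: Φ(0.167/√(2 × 0.96/191) − 1.96) | 0.38 |
| 55.4% drinkers, r = 0.6 | 0.45 |
| 55.4% drinkers, r = 0.8 | 0.76 |
| 70% drinkers, r = 0.2 | 0.43 |
| 80% drinkers, r = 0.2 | 0.66 |
| 55.4% drinkers, r = 0.2, CV among drinkers 0.5 | 0.17 |
| 55.4% drinkers, r = 0.2, CV among drinkers 1.0 | 0.11 |

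The last two rows use an overall CV of √((1 + c²)/p − 1), where c is the CV among drinkers. That is 1.12 for c = 0.5 and 1.62 for c = 1.0.

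**The case against.** **The two-drink figure is inferred.** This stands. The means may sit in a figure or table that is not shown. Sample size and power alone do not identify the pattern: differences of (0, 2, 0) or (0, 1.15, 2.31) also give 0.90. Those patterns, however, give a partial η² for group of 0.009 and 0.028 rather than 0.037, so (0, 2, 2) is the best supported. It still relies on assumed time means and on reading the printed *f* values as partial η².

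**A reader might infer that the trial can never have more than 25% power for 15%.** The documents do not support that. The figure holds for r = 0.2, 191 completers per group, the interaction test and 55.4% drinkers. The bound also pairs identical drinkers with r = 0.2, an uneasy combination: if abstainers stay abstainers, r would be high, and at r = 0.9 the bound is 0.97. Real drinkers vary, which pulls the other way: with c = 1.0, power at r = 0.8 is 0.30. But r = 0.2 is the protocol's own planning value.

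**55.4% is a survey figure, not a design assumption.** This stands. Volunteers may drink more, and low use is not zero use. Even so, 90% at r = 0.2 needs at least 87.7% drinkers who all drink alike.

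**A reader might infer that the protocol plans only a within-arm comparison.** It does not: section 2.2 names the control group and two time points. Only the wording of the 15% itself is loose.

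**No printed calculation is wrong.** Correct: 191, 0.90 and 764 all reproduce. The fault lies in what the 90% is taken to describe.

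**Conclusion.** The concern holds in conditional form. The stated 90% power is not the power for the primary hypothesis as section 2.2 words it. It fits a difference of about 2 drinks, which is 15% only at a mean of about 13.3, and SD 5 cannot go with that mean if anything like 44.6% of participants score zero. At the cited prevalence, with the protocol's r and n, power for a 15% reduction in the interaction test is at most about 25%. Other analyses, a higher correlation or more drinkers raise the ceiling, as tabulated; variation among drinkers lowers it.

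The conclusion assumes alpha 0.05, a sample that resembles the cited survey and, for the two-drink figure only, the back-calculated means. The 0.167 SD bound does not depend on SD 5 or on those means.

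**What to change.** **Section 2.5.1.** Print the hypothesised means that were actually used, and say which absolute difference the 90% refers to. Report separately the power for a 15% reduction, or the detectable percentage reduction, over a range of mean, SD and r that allows for non-drinkers. Take the inputs from the 2020 pilot of 60 students if drinking was recorded there (the article reports no such values), and from T0 data pooled across arms once available.

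**Section 2.2.** Remove 'up to', and state the 15% as a between-group contrast at a named time point.

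**Reporting.** Interpret a non-significant result through its confidence interval, not as evidence of no effect. Whether 15% can be ruled out will depend on the interval obtained.

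**Cost.** Rewording and a rerun of the power calculation. The stated power becomes less favourable. No extra participants are required.

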### Participants and recruitment

2.3

For the RCT, undergraduate or graduate students will be recruited from participant universities. Inclusion criteria include being an adult over 18 years of age, agreeing to be randomly assigned to either intervention or comparison group and being able to read Spanish. Year of school, department/university, socioeconomic status, and gender will be measured as control variables. For recruitment, 103 Colombian universities have been invited to participate, through presentations and emails. Some universities will need a formal agreement outlining the particulars of the intervention and how assessments among participants will be done; others will extend the invitation to students for them to participate by themselves. Multiple strategies will be used to recruit participants; they will include a call for participation sent by the universities, through social media, institutional emails, and promotional videos. Invitations will include the link for registration, where we will ask for name, email, and phone number. The information will be hosted in the [Corporación Nuevos Rumbos] server with only the research team having access. The researchers will contact the registered participants and give detailed information about the procedure and send informed consent forms for participation, inviting them to accept or refuse the intervention. The consent form specifies that the collected information will be confidential, that it will be used for the intervention and research goals, and that they will be randomly assigned to either IBEM-U or EDA. Individuals participating in other alcohol prevention program will be excluded. As the intervention is online, contamination is considered unlikely. Those students who agree to participate will receive a link to fill out the measurement instruments and schedule an appointment for the first meeting on one of the two programs.

### Intervention trial

2.4

#### IBEM-U

2.4.1

The program is based on motivational principles as used in Motivational Interviewing [25]; 2013; [26], and the I-Change Model [30].

IBEM-U is an adaptation for university students of the version for secondary adolescents comprised of two 20-min sessions that are three months apart. The process is highly interactive, in which the student and facilitator are continuously exchanging information, questions and suggestions. Every meeting requires participants to fill out two questionnaires before they start the session. These instruments will measure alcohol use and level of risk due to their pattern of consumption, as well as the I-Change Model components (for more detail, see the measures section). During the intervention, a trained facilitator will guide the student throughout the six steps described in Table 1, Table 2. The same will happen in the second meeting, but the goal and topics of conversation are different. The reader can find the step-by-step guide of the intervention with the related tools and examples in the complete manual at [www.nuevosrumbos.org].

**Table 1 tbl1:** Steps to be followed during the first session of the program.

STEPS	
1. *introduction and orientation to the program:* The facilitator introduces him/herself, discusses the goal of the intervention, and confirms the informed consent and the sociodemographic data.	4. Importance and confidence scales*:* The facilitator asks the participant to rank how important it is to them to maintain low-risk alcohol assumption on a scale from 1 to 10. The facilitator discusses the participant's answer to determine the main motivations for making a change. Then he or she asks the participant to also rank their confidence to make a change or maintain a low-risk consumption from 1 to 10.
2. *Risk level:* The facilitator revises the risk level delivered by the system, based on the answers related to alcohol use prevalence and to the AUDIT instrument (WHO, 2000). The options of risk level are Low, Medium, High, or Severe, and it is displayed on the screen of the participant in form of pyramid. The facilitator explains why the participant is placed in this level and continues with the interview.	5. *Self-imposed goal and strategies:* The participant is guided to propose an action plan composed of a goal regarding alcohol use and several strategies to achieve it. The user is responsible of determining what, how and when he/she will do it.
3. *Evocation and motivators:* Answers to the AUDIT and other questions related to consumption patterns from the interview are used to discuss alcohol use in more depth. Attitudes, practices, experiences, and other perspectives about alcohol use are identified. Any myths about consumption that arise will be clarified. All this information is stored in an electronic platform. Then the facilitator asks about other activities such as free time and short- and medium-term plans. Using this information, the facilitator focuses the intervention on salient physical or psychosocial risks. Facilitator's feedback is personalized based on the conversation between the facilitator and the participant.	6. Summary: the last step of the intervention is discussing with three final questions with the participant: 1. What are the obstacles to achieving the goal? 2. What strategies can be used to cope with difficulties that arise? 3. What are the advantages of maintaining low-risk consumption?

**Table 2 tbl2:** Steps to be followed during the second session of the program.

STEPS	
1. *introduction and orientation to the program:* The facilitator introduces him/herself, discusses the goal of the intervention, and confirms the informed consent and the sociodemographic data. The goal of this meeting is different to the first one, it is to do a balance of the process.	4. I*mportance and confidence scale:* The professional asks: in a 1 to 10 points scales, where 1 is “not at all” and 10 is “very important”, how important is for you to maintain a low-risk alcohol consumption? The facilitator inquiries about the choice to determine what are the main aspects to make a change. Then, he asks the same but with a scale of confidence to make a change or maintain a low-risk consumption.
2. *Summary and Risk level:* The facilitator summarizes the past session and determines the risk level to be used for the session based on the answers related to alcohol use prevalence and to the AUDIT instrument (WHO, 2000). He/she communicates the risk level and informs the reasons why the participant is placed in this level of the intervention to continue with the interview.	5. *Monitoring the process:* The participant is asked about changing or maintaining the same action plan based on his/her new answers and the barriers and facilitators identified during both sessions.
3. *Goal achievement:* Every participant is asked about the achievement of the goal he or she created at the end of the previous session. Barriers and facilitators to achieving the goal will be discussed.	6. *Summary*: A synthesis of the process is presented to the participant; the goal of this step is to increase self-efficacy. Not only verbal but non-verbal communication is important for them to fulfill their goals.

